## Abstract

**Introduction::**

Despite increasing evidence that aerobic exercise and cognitive training improve cognitive function among patients with cognitive impairment and dementia, few studies have focused on the effect of a combination of these approaches. This study will explore whether combining aerobic training (AT) with mindfulness training (MT), an intervention promoting the moment-to-moment awareness of physical sensations, affective states, and thoughts, improves cognitive function in individuals at risk of dementia. The primary objective is to determine the feasibility and acceptability of the intervention(s). The secondary objective is to obtain estimates of effect sizes on cognitive function and on possible mediators.

**Methods and analysis::**

Forty participants with at least 2 risk factors for dementia will be randomized (2 × 2 factorial design) to either AT (3 sessions/week for 12 weeks), MT (1 session/week for 8 weeks), both, or usual care. Assessments of cognitive function (attention, executive function, episodic, and working memory); physical activity (accelerometry), aerobic capacity (6-minute walk test), waist-to-hip ratio, blood pressure, social support (Multidimensional Scale of Perceived Social Support), depression (Hospital Anxiety and Depression Scale), and mindfulness (Five Facets of Mindfulness) will be conducted at baseline, end of treatment, and 6-months postbaseline. Rates of retention, attendance, and program satisfaction will be calculated for each of the 4 groups to determine the feasibility and acceptability of each intervention.

**Ethics and dissemination::**

This study has full ethical approval by The Miriam Hospital Institutional Review Board and adheres to the Standard Protocol Items: Recommendations for Interventional Trials reporting recommendations. If results from this exploratory, proof-of-concept study support our hypotheses, we will conduct a large randomized controlled trial (RCT) to determine the efficacy of combined MT and AT in improving cognitive function in individuals at risk of dementia. Results from the study will be disseminated through peer-reviewed journals and conference presentations.

**Registration details::**

http://www.clinicalstrials.gov identifier NCT03289546.

## Introduction

1

In 2014, 5.2 million Americans had Alzheimer disease.^[1]^ Due to longer life expectancy and demographic changes, prevalence rates of dementia are projected to increase nearly 4-fold in upcoming decades. There is currently no effective pharmacological treatment to reduce the risk of dementia and age-related cognitive impairment or improve the disease course.

Although pharmacological treatments are under study, increasing attention has been dedicated to preventive and behavioral strategies. Interest in behavioral approaches stems from findings suggesting that up to a 3rd of Alzheimer disease cases worldwide may be attributable to modifiable risk factors^[2]^ and that improvements in cognitive and physical inactivity in midlife could prevent up to 3 million dementia cases.^[3]^ Strong observational evidence indicates that physically^[4–9]^ and cognitively stimulating^[10–13]^ activity may prevent cognitive decline or dementia. In contrast, evidence from randomized clinical trials (RCTs) is less clear, and reveals that improvements from cognitive training are limited to training-specific domains, with little evidence that benefits generalize to other cognitive capabilities or translate into meaningful improvements in activities of daily living.^[14–17]^ For exercise, findings from RCTs and meta-analyses indicate that aerobic exercise produced small to moderate improvements in cognitive function among patients with mild cognitive impairment and dementia, while no effect has been observed among healthy individuals with no cognitive impairment at baseline.^[18–21]^

Few studies have focused on the effect of combined cognitive and aerobic training (AT).^[22,23]^ A 2 × 2 RCT of cognitive training and aerobic activity found no difference between intervention and control participants but used very active control conditions.^[23]^ A 2nd small RCT suggested that combined aerobic and cognitive training could produce larger effects than either technique alone.^[24]^ Evidence from fMRI imaging studies also indicates that combined approaches may increase brain plasticity.^[25]^

Mindfulness training (MT) is a behavioral intervention designed to increase mindfulness, the “nonjudgmental, sustained, moment-to-moment awareness of physical sensations, affective states, and thoughts.”^[26]^ MT, which is essentially an intensive attention-training intervention,^[27]^ has shown potential to improve attention and working memory by increasing the ability to override irrelevant stimuli.^[28]^ These effects emerged across populations, with RCTs comparing MT to control conditions resulting in improved working memory capacity among middle school and graduate students, as well as military personnel.^[29–31]^ Additionally, experienced mindfulness meditators perform better on assessments of attention compared to controls without meditation experience.^[32]^ Another RCT showed significant improvements in executive functioning in older adults who completed 8-weeks of MT compared to wait list control.^[33]^

Taken together, this evidence supports the potential for a beneficial effect of approaches combining AT and MT. No study thus far has explored the possible cumulative effect of MT and AT on cognitive function. This proof of concept study, titled the Active Minds Study (NCT number 03289546), is proposed in preparation for a future large efficacy RCT with the primary outcome of determining whether the combination of MT and AT is feasible and acceptable. The study will also explore whether a combined MT and AT intervention improves cognitive function, and whether improvements in aerobic capacity, physical activity, cardiovascular risk factors, and mindfulness skills are associated with changes in cognitive function. This work was supported by a grant from the Norman Prince Neurosciences Institute to Drs [name] and [name]. The Standard Protocol Items: Recommendations for Interventional Trials guidelines were followed in reporting the protocol for this ongoing study.^[34,35]^ Participant recruitment began April 2016 and the study is expected to be completed by December 2018.

## Methods and analysis

2

### Study design and setting

2.1

This study utilizes a 2 × 2 factorial design. Participants are randomly assigned to MT, AT, both treatments, or neither (see Fig. 1). Study assessments and MT sessions are conducted at the Centers for Behavioral and Preventive Medicine at the Miriam Hospital in Providence, RI, while AT sessions are held at a local YMCA.

**Figure 1 F1:**
[figure not shown]
Active minds study design. AT = aerobic training, MT/AT = both conditions (mindfulness training/aerobic training), MT = mindfulness training, UC = usual care.

### Population

2.2

This study will enroll 40 patients (10 per condition). Inclusion criteria are: At least 2 risk factors for dementia; Age ≥55; Being physically inactive (defined as not meeting current AHA recommendations for physical activity, that is, <150 minutes of moderate-intensity aerobic activity per week OR < 75 minutes of vigorous aerobic activity per week using the 7-day Physical Activity Recall Questionnaire)^[36–40]^; English fluency; and Ability to understand the study procedures and willingness to commit to the demands of the study protocol. Exclusion criteria include: Inability or unwillingness to provide informed consent; Contraindications to physical activity; Blood pressure >200/110 measured at screening visit; Severe depressive symptoms (Hospital Anxiety and Depression Scale depression subscale score >14)^[41]^; History of psychosis; Severe cognitive impairments (Mini-Mental State Examination score < 24)^[42]^; Hospitalization in the previous 6 weeks; and Current (at least once a month) practice of mindfulness meditation, yoga, or tai chi. In addition, the participant's primary care provider (PCP) written permission to participate in the study is required. This study protocol was approved by The Miriam Hospital Institutional Review Board (IRB).

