#### Screening assessments

2.7.1

The 7-day Physical Activity Recall Questionnaire^[36]^ is used to determine physical activity status for screening purposes. Patients are considered physically inactive if they do not meet current recommendations (<150 minutes of moderate-intensity aerobic activity per week OR < 75 minutes of vigorous aerobic activity per week).^[37–40]^ This measure is also administered at 3 and 6 month assessments as a backup in case of accelerometer failure.

The Mini Mental State Examination^[42]^ is used to screen for severe cognitive impairment, with participants scoring less than 24 excluded from the study.

Blood pressure is measured using a Dinamap XL automated blood pressure monitor according to current recommendations.^[46]^ Participants with blood pressure >200/110 or symptomatic orthostatic blood pressure decrease of >20 mm Hg are excluded from the study and referred to their PCP for follow-up.

Depression is assessed with the 7-item depression subscale of the Hospital Anxiety and Depression Scale.^[41]^ Subscale scores range from 0 to 21, with higher scores indicative of greater depressive symptoms. Participants with depression subscale scores >14 are excluded from the study and referred to their PCP.

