### Statistical analyses

2.8

Our choice of sample size (n = 40, 10 participants per condition) was determined by the scope and timeline of this project. Given that this is a proof of concept study, our focus is not on strict hypothesis testing but rather on estimates of effect size and corresponding confidence intervals.

Depending upon variable characteristics (categorical or continuous), Fisher exact test or *t* tests will be used to compare participants at baseline on socio-demographic and medical characteristics. Baseline characteristics not balanced by randomization, as well as variables associated with the study outcomes, will be included as covariates in linear or logistic regression analyses.^[58,59]^

Rates of retention and attendance, as well as program satisfaction scores at 3 and 6 months will be calculated separately for each of the 4 groups. The study will be considered feasible if retention rates of at least 80% are achieved, if participants attend at least 70% of the planned sessions, and if they report completion of at least 70% of the assigned individual home practice exercises. For acceptability, each intervention will be considered acceptable if at least 80% of participants indicate grade 4 enjoyment ratings on a visual scale ranging from 0 to 4.

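### The spelled-out rule for physical inactivity joins its two thresholds with OR and so does not match the definition it is meant to express

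*Protocol article*

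**What the plan says.** Section 2.2 (Population) sets the inclusion criterion in two parts. The governing definition is "Being physically inactive (defined as not meeting current AHA recommendations for physical activity, that is", and the rule that follows it is "<150 minutes of moderate-intensity aerobic activity per week OR < 75 minutes of vigorous aerobic activity per week". Section 2.7.1 (Screening assessments) repeats the same structure and applies the inactive label when "they do not meet current recommendations (<150 minutes of moderate-intensity aerobic activity per week OR < 75 minutes of vigorous aerobic activity per week". The instrument is fixed as well: "The 7-day Physical Activity Recall Questionnaire^[36]^ is used to determine physical activity status for screening purposes". The article does not reproduce the recommendation itself, and does not say how moderate and vigorous minutes are to be combined.

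**The concern.** The definition is a negation: inactive means not meeting a recommendation. Two thresholds for two intensities read most naturally as alternative ways of meeting one recommendation. A person fails an either/or requirement only by failing both branches, so the negation needs AND. The article carries OR over into the negated rule, in both places where the rule is stated.

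Three things are at stake.

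- **Population.** The criterion may not deliver the inactive group that the trial says it studies.
- **Eligible count.** Section 2.7.2 lists the number of eligible participants among the primary feasibility measures. This rule feeds directly into that count, and so into the recruitment yield carried forward to the larger trial.
- **Activity contrast.** Physical activity and the 6-minute walk are posited mediators (2.7.4), and 2.8 plans to estimate group effects on mediators at 3 months. People who are already active leave aerobic training less room to change their activity, which would narrow that contrast.

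**Working it through.** No sample-size, power or error-rate figure is involved, so there is no plan figure to reproduce. The check is one of logic.

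**Inputs.** Let M and V be weekly minutes of moderate and vigorous aerobic activity on the 7-day Recall. The thresholds are 150 and 75 (2.2 and 2.7.1). The written rule is: inactive if M < 150 or V < 75.

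**Step 1: negate each possible form of the recommendation.**

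- Form A, either threshold suffices: met if M ≥ 150 or V ≥ 75. Its negation is M < 150 **and** V < 75.
- Form B, both thresholds required: met if M ≥ 150 and V ≥ 75. Its negation is M < 150 **or** V < 75.

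The written rule is the negation of Form B, not of Form A.

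**Step 2: apply both rules to test cases.**

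| M | V | Inactive as written (OR) | Inactive with AND |
|---|---|---|---|
| 0 | 0 | yes | yes |
| 100 | 30 | yes | yes |
| 149 | 74 | yes | yes |
| 150 | 0 | **yes** | **no** |
| 200 | 0 | **yes** | **no** |
| 300 | 0 | **yes** | **no** |
| 0 | 75 | **yes** | **no** |
| 0 | 100 | **yes** | **no** |
| 150 | 75 | no | no |

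The rules differ for everyone who reaches exactly one threshold. As written, a person escapes the inactive label only by reaching both.

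**Step 3: which form is more plausible?** Under Form B, the least activity that counts as meeting the recommendation is 150 + 75 = 225 minutes a week, 75 of them vigorous. A person with 300 moderate minutes would then be called inactive. That sits badly with the ordinary meaning of the term, so Form A is the better reading. It remains an assumption.

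**Step 4: does another stated step exclude such people?** In 2.4 the accelerometer is worn during the run-in to assess baseline activity, but no eligibility cut-off is attached to it. Primary care clearance does not test activity level. Among the other criteria in 2.2, the exclusion of current mindfulness, yoga or tai chi practice would not catch someone whose activity is, for example, walking. Nothing else stated addresses the amount of activity.

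**Step 5: direction of the correction.** Everyone with M < 150 and V < 75 also satisfies M < 150 or V < 75. The AND rule therefore selects a subset of those eligible under OR. Re-scoring can only remove people, and nobody excluded under the written rule becomes eligible.

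**The case against.** The strongest reply is that the governing phrase already points the right way. The thresholds are a gloss on it, and staff who applied the phrase itself would have turned away anyone meeting the recommendation. This stands in part. The fault is a contradiction inside one criterion, and a reader who infers that active people were in fact enrolled goes further than the article allows, since it reports no screening results. But the gloss is the only numerical rule given, and it is the one a person scoring the Recall would use.

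A second reply is that the recommendation is not reproduced, so OR might be the correct negation. This also stands as a limit: the point depends on Form A. Even so, the text does make eligible a person well above 150 moderate minutes.

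A third reply is that the harm is small. Baseline activity is recorded by accelerometer, outcome models control for baseline, unbalanced characteristics become covariates (2.8), and the trial is a proof of concept: "Our choice of sample size (n = 40, 10 participants per condition) was determined by the scope and timeline of this project". These features make active entrants visible and limit hidden bias. They do not restore the intended population or correct the eligible count.

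Two stronger inferences should be resisted. A reader might suppose that active entrants inflate attendance and retention. Nothing in the article shows this, and mindfulness attendance or usual-care retention has no evident link to baseline activity. A reader might also want a combined score that counts vigorous minutes double. The article states no such equivalence, and the score would be a different criterion: M = 100, V = 30 is inactive under AND but gives 100 + 2 × 30 = 160, above 150.

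**Conclusion.** The point holds as a contradiction between the definition and its spelled-out rule, present in both 2.2 and 2.7.1. It assumes that either threshold alone meets the recommendation. On that assumption, the literal rule wrongly makes eligible everyone who reaches exactly one threshold, and no other stated step excludes them. How many such people were screened or randomized cannot be derived from the article and may be none. The possible effects are on who is studied, on the eligible count and on the activity contrast for aerobic training. Severity is moderate: this is an operative eligibility rule that should be corrected, but it does not undermine the design.

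**What to change.** In 2.2 and 2.7.1, after checking the cited recommendation, join the thresholds with AND: fewer than 150 moderate minutes and fewer than 75 vigorous minutes per week. Use this one rule throughout.

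Re-score the stored screening Recalls of those judged eligible by the same rule. This presumes that moderate and vigorous minutes were recorded separately, as the existing rule already requires. Report how many randomized participants fail it, and in which groups. Keep everyone in the main intention-to-treat analysis, and add a descriptive sensitivity summary that leaves out those who fail. With 10 per group it should be read as description only. If the count is zero, one sentence saying so closes the matter.

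The cost is a wording amendment through the IRB, re-scoring of data already held and, for any recruitment still to come, a few more screen failures.

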### Recruitment

2.3

We will have 2 cycles of intense recruitment efforts in order to enroll about 20 participants per recruitment cycle. Recruitment approaches include: Flyers placed in clinics and local public venues (eg, libraries, supermarkets); Advertisements in local newspapers; and Online resources (eg, The Miriam Hospital Intranet, Craigslist, and social media).

### Screening and consent procedures

2.4

Initial contact is made via telephone by interested individuals using a dedicated phone number included in all recruitment materials. Patients signaling interest are then invited for a screening visit.

Full informed consent and HIPAA authorization is obtained in person by the senior research assistant (SRA) after a thorough explanation of the study design, study intervention, and the risks and benefits involved. After informed consent procedures are completed, participants undergo a battery of screening assessments (see Study Assessments for details).

Following the screening visit, patients enter a 2-week run-in period during which they wear accelerometers for the assessment of baseline level of physical activity and obtain clearance for participation from their PCP. Accelerometers are fitted during the screening visit and returned via mail using a prestamped envelope.

Information is collected from all individuals assessed for eligibility (ie, individuals who consented but then resulted noneligible at the completion of the screening process) in order to provide a complete CONSORT diagram and description of the recruitment process. This information will also serve as an indicator of future generalizability of the study.

Once all screening assessments are completed participants are randomly assigned (1:1:1:1 ratio) to the 4 different conditions. The randomization schedule was generated in “R” (cran.us.r-project.org) and is based on a permuted block randomization scheme with small, random-sized blocks. The allocation table was uploaded to an ACCESS database to conceal the sequence and the SRA performs randomization by clicking the “randomize” button.

Participants are not blinded to treatment allocation, but are blinded to the study hypothesis. For practical reasons, the MT instructor cannot be blinded, however s/he is not be involved in data management or analysis. Blinded personnel include the Principal Investigator, co-investigators, and all data entry and analysis personnel.

### Study interventions

2.5

Participants assigned to Mindfulness Training (MT) alone receive MT based on the curriculum of the manualized Mindfulness-Based Stress Reduction (MBSR) program created by Jon Kabat-Zinn at the University of Massachusetts.^[26]^ Participants attend an orientation session during which they are introduced to the purpose, content, and schedule of the intervention, followed by one two and a half-hour MT sessions once a week for 8 weeks. The MT protocol includes the following basic components of traditional MBSR programs: training in awareness of sensations (“body scan”), a technique based on the cultivation of attention to bodily sensations that normally go unnoticed; training in the awareness of the sensations of breathing; training in directing the attention to simple activities of daily life, and in recognizing when the attention is no longer focused on a specific object of attention; and training in “open awareness”, a practice in which participants are instructed to just notice to which event (physical sensation, sound, visual object, and thought) their attention is spontaneously drawn from moment to moment. The MT instructor is a graduate of the teachers’ training program at the University of Massachusetts Center for Mindfulness with ≥5 years teaching experience.

In addition to MT sessions, participants are instructed to practice mindfulness techniques for 30 minutes daily on their own with the guidance of a digitally recorded, standardized guided mindfulness practice. The recording is provided in different formats (CD or MP3 file) depending on the participant's preference; CD players are offered to participants who do not possess 1 and MP3 versions are uploaded onto the patient's smartphone or other device.

Participants assigned to aerobic training (AT) alone attend a 1-hour AT session 3 times per week for 12 weeks. Sessions consist of a 10-minute warm-up, 40 minutes of aerobic exercise (walking on a treadmill), and 10 minutes of cool down and stretching. Participants receive heart monitors at the beginning of the study and are trained to exercise targeting heart rates at 65% to 75% of the age predicted max heart rate or at an intensity of 12 to 13 in the Borg scale of the rate of perceived exertion. Exercise sessions are supervised by a Master's level (Kinesiology) instructor.

Participants assigned to the MT + AT condition attend 2 AT sessions and 1 MT session every week for 8 weeks, followed by 3 AT classes per week for 4 additional weeks. Participants are encouraged to participate in as many sessions as possible and are contacted by the SRA each week to remind them of their weekly classes.

Participants assigned to neither intervention continue with the care prescribed by their physicians. To increase retention, at study completion these participants will receive a voucher to attend the YMCA free for 3 months as well as a copy of the MT practice recording.

Although participating in the study, all participants are allowed to continue all medications and treatments (ie, dietary recommendations) prescribed by their care providers. However, participants, regardless of group assignment, are prohibited from engaging in yoga, tai chi, or other mind-body training while enrolled in the study.

To increase overall study retention, patients are asked to provide a home and mobile phone number and email address. The study tracking system identifies participants due for a visit and mail/email reminders or phone messages are then sent to remind patients of their follow-up appointments or class sessions. In addition, we provide a $40 monetary incentive at each of the 3 assessment visits (baseline, 3 month, and 6 month), as well as small gifts such as water bottles and heart monitors. To avoid bias, no incentive is provided to facilitate participation in intervention sessions.

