### Strengths and limitations

3.1

This is the first study to investigate the effects of AT, MT, and their combination in older adults at risk for dementia. By utilizing a 2 × 2 factorial design, we will be able to describe the role of AT and MT on cognitive function and to determine if the combination may produce effects greater than either intervention alone.

Many prior studies examining the effects of AT and mindfulness-based approaches on cognition, used singular outcome measures such as the Mini-Mental State Examination to describe overall, global cognitive functioning. Although less demanding on researchers and participants, such an approach precludes a more nuanced understanding of the effect on different aspects of cognition. For this study we chose to administer a battery of measures to assess cognitive function across several domains. This comprehensive approach will help explore whether the posited benefits of AT, MT, and MT + AT are domain-specific or extend across domains. Last, this study is also strengthened by rigorous assessments of treatment fidelity throughout delivery of the interventions.

We acknowledge that the interventions proposed in this study are both time and labor-intensive. Participants are asked to contribute between 3 and 4 hours per week over the course of 8 to 12 weeks, not including travel time or time taken to complete study assessments. This schedule was chosen to ensure that participants receive a strong enough “dose” of each intervention and to be as consistent as possible with the structure of the MBSR program.

Detailed feedback will be obtained from participants regarding the length, structure, and quality of all aspects of the MT and AT interventions, and their input will be carefully considered in determining the format of the interventions that will be used in future studies. One possible modification could be to deliver MT using a mobile app instead of requiring participation in class-based sessions, which has the potential to significantly reduce participant burden. Another limitation is the small sample size of this study, as such, results will be only preliminary, and will be used to inform a larger RCT designed to establish the efficacy of this approach.

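### The combined arm is scheduled for 28 aerobic sessions against 36 in the aerobic-only arm, so MT+AT versus AT compares two packages and does not isolate the effect of adding mindfulness training

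*Protocol article*

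**What the plan says.** All references are to the protocol article.

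- **Section 2.1 (Study design and setting):** "This study utilizes a 2 × 2 factorial design". The arms follow: "Participants are randomly assigned to MT, AT, both treatments, or neither". No schedule is given there.
- **Abstract (Methods and analysis):** participants are randomised "to either AT (3 sessions/week for 12 weeks), MT (1 session/week for 8 weeks), both, or usual care". The combined arm is named in one word, without a schedule of its own.
- **Section 2.5 (Study interventions), AT alone:** "Participants assigned to aerobic training (AT) alone attend a 1-hour AT session 3 times per week for 12 weeks". Each session contains "40 minutes of aerobic exercise (walking on a treadmill"), with a warm-up and a cool-down.
- **Section 2.5, MT alone:** one session of two and a half hours a week for eight weeks, plus daily home practice.
- **Section 2.5, combined arm:** "Participants assigned to the MT + AT condition attend 2 AT sessions and 1 MT session every week for 8 weeks", and then three AT classes a week for four more weeks.
- **Section 2.8 (Statistical analyses):** one mixed model compares MT+AT with MT alone, with AT alone and with neither, to give effect sizes and confidence intervals.
- **Section 3.1 (Strengths and limitations):** the factorial design is credited with describing the role of each component and with the ability "to determine if the combination may produce effects greater than either intervention alone". The Discussion gives the aim as exploring possible synergy.

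The limitations in section 3.1 cover participant burden and small sample size. They do not mention that the amount of AT differs between the two AT arms.

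**The concern.** A 2 × 2 factorial supports statements about components because each factor means the same thing at both levels of the other. MT+AT minus AT can then be read as the effect of adding MT, and the difference between the two AT effects (with and without MT) can be read as interaction. Under the section 2.5 schedule the AT factor changes when MT is present, so those readings are not available without a caveat.

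The affected contrast, MT+AT versus AT alone, is one that section 2.8 plans to estimate. It also bears on the expectation in section 2.7.3 that the combination will do better than either component alone. The trial exists largely to hand effect sizes and a theoretical framework to a larger RCT. If this contrast is passed on as the added value of MT, the next trial inherits a mislabelled quantity, and a larger sample will not correct that. The Discussion criticises tai chi research for being unable to separate its active ingredients; this schedule brings back part of the same difficulty.

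**Working it through.** The article states no session totals, so there is no figure to reproduce. The counts follow from the schedules in section 2.5.

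**AT sessions**

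| Arm | Weeks 1–8 | Weeks 9–12 | Total |
|---|---|---|---|
| AT alone | 3 × 8 = 24 | 3 × 4 = 12 | 36 |
| MT+AT | 2 × 8 = 16 | 3 × 4 = 12 | 28 |
| Difference | 8 (33%) | 0 | 8 (8/36 = 22%) |

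In aerobic minutes at 40 per session: 36 × 40 = 1,440 against 28 × 40 = 1,120, a gap of 320.

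**MT sessions:** 1 × 8 = 8 in MT alone and 8 in MT+AT. This component is scheduled equally.

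**What each contrast holds constant**

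- MT+AT versus AT: adds 8 MT sessions and removes 8 AT sessions. Two things change.
- MT+AT versus MT: MT is 8 sessions on both sides. It isolates adding AT, at 28 sessions.
- MT versus usual care: isolates MT at 8 sessions.
- AT versus usual care: isolates AT at 36 sessions.

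**Illustrative size.** The article gives no effect size or dose-response, so these are assumptions: the AT effect is linear in sessions, AT and MT are additive with no true interaction, *d* is the effect of 36 AT sessions and *m* the effect of MT. The arm means relative to usual care are then *m* (MT), *d* (AT) and *m* + (28/36)*d* (MT+AT).

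- MT+AT − AT = *m* − (8/36)*d* = *m* − 0.22*d*
- Interaction = (MT+AT − MT) − (AT − usual care) = (28/36)*d* − *d* = −0.22*d*, although none was assumed
- Offset for *d* = 0.2 SD: −0.04 SD; for 0.3: −0.07; for 0.5: −0.11

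**Set against the precision.** With 10 per arm, an unadjusted normal approximation gives a 95% half-width for a pairwise difference of 1.96 × √(2/10) = 0.88 SD. Over *d* = 0.2 to 0.5 that is roughly 8 to 20 times the offset.

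**The case against.** The strongest reply is that the trial does what it says. The combined schedule is stated openly in section 2.5. Randomisation makes MT+AT versus AT a fair comparison of the arms as delivered, so the question whether the combination beats either intervention alone can be answered at any AT dose. The cognitive aims are secondary, are about estimation rather than testing, and are described as preliminary. Section 3.1 acknowledges the time burden and links the schedule to adequate exposure and to the MBSR structure, so the reduction may be deliberate. All of this stands, and it limits the point to interpretation. It does not supply the missing caveat: the article rests component claims on the factorial label and nowhere says that the AT component differs between arms.

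Four stronger readings are tempting, and the article does not support them:

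- **The abstract contradicts section 2.5.** The abstract defines the AT and MT schedules and then uses only a short label for the combined arm. A reader may infer the full AT schedule there, but it is not stated. The abstract is imprecise.
- **Planned main effects and an interaction test are biased.** Section 2.8 plans pairwise comparisons of four groups. No pooled main effect or interaction contrast is specified, so that confounding arises only if such a quantity is derived later.
- **Only comparisons with usual care are clean.** MT+AT versus MT holds MT constant and does isolate AT, at the lower session count.
- **The two AT arms are matched on total sessions (36 and 28 + 8 = 36).** The lengths differ: class time is 36 × 1 = 36 hours for AT alone and 28 × 1 + 8 × 2.5 = 48 hours for MT+AT, before home practice.

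**Conclusion.** The point holds as one of design description and interpretation. The schedule does not deliver the constant AT factor that the factorial label implies. Of the contrasts discussed, only MT+AT versus AT is both planned and affected: it estimates replacing 8 of 36 AT sessions with 8 MT sessions, not adding MT. A synergy estimate or pooled main effect derived later would be confounded with AT dose. The counts (28 against 36, −22%) are certain from the stated schedules.

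The size of any effect on the estimate is not certain. The figure of −0.22*d* depends on linearity and additivity, its direction depends on more AT being beneficial, and it is small beside the imprecision at 10 per arm. A reader might infer that the trial is invalid or that its main conclusions are biased. That does not follow: the randomised comparison is sound, and feasibility and acceptability, the primary outcomes, are not biased by the difference. The correction is still worth making, because it changes what may be concluded about MT and about synergy, and what is handed to the larger trial.

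**What to change.** Reconcile the factorial description in the abstract and sections 2.1 and 3.1 with the schedule in section 2.5. Which schedule is intended is for the investigators to say.

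If the section 2.5 schedule stands:

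1. Describe MT+AT as a modified package, not simply as both treatments.
2. Label MT+AT versus AT as a package comparison in which 8 MT sessions replace 8 of 36 AT sessions. State that MT+AT versus MT estimates AT at 28 sessions.
3. Qualify the claims about component roles and synergy in the Discussion and section 3.1, and list the unequal AT dose as a limitation.
4. Show the number of AT sessions attended, by arm, beside the MT+AT versus AT estimate. Attendance is already logged, but section 2.8 reports it as rates, which conceal different denominators: 70% attendance is 0.70 × 36 = 25.2 AT sessions in one arm and 0.70 × 28 = 19.6 in the other.

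Under that schedule the cost is wording and one extra line in a table, with no change to sample size, randomisation or the model. The downside is a weaker claim about synergy.
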